### Outcome Evaluation and Analysis

Participants in both arms will complete the following clinically validated questionnaires at baseline: State-Trait Anxiety Inventory (STAI) [27], Quality of Life Enjoyment and Satisfaction Questionnaire-Short Form (Q-LES-Q-SF) [28], Generalized Anxiety Disorder-7 item (GAD-7) [29], Depression Anxiety Stress Scale-42 item (DASS-42) [30], and a demographic questionnaire. All questionnaires will be completed through OPTT. The STAI, Q-LES-Q-SF, GAD-7, and DASS-42 will be completed again during week 6 and week 12. Using data from previous research incorporating this e-CBT program, a sample of 50 participants in each group was determined to be sufficient for an effect size of 0.5, a power of 0.8, and an α of .05 [31].

Before analysis, the data will be examined for missing, nonsensical, and outlying variables. Missing data will be removed on a per-protocol basis, with a statistical analysis significance level set at .05. Demographic information (ie, age, gender, and race) will be assessed between groups and program noncompleters using independent sample *t* tests. A 2×3 repeated measures ANOVA will be completed for each questionnaire score at the time points to investigate the differences between the 2 groups. An intention-to-treat analysis will be completed to assess whether the outcome of treatment impacts participants’ likelihood of not completing the program. Data will also be assessed with linear mixed-effects models with random effects as patient identification and fixed effects as treatment, time, and their interaction. SPSS (version 24; IBM Corp) will be used for all statistical analyses.

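### The only stated baseline comparison of noncompleters covers age, gender and race, so it says little about severity-related attrition, although four baseline severity and quality-of-life scores are already collected

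*Protocol article*

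**What the plan says.** All of the relevant text is in the protocol article, Methods, Outcome Evaluation and Analysis.

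- Baseline data: "Participants in both arms will complete the following clinically validated questionnaires at baseline", followed by STAI, Q-LES-Q-SF, GAD-7, DASS-42 and a demographic questionnaire.
- Follow-up: "The STAI, Q-LES-Q-SF, GAD-7, and DASS-42 will be completed again during week 6 and week 12".
- Missing data: "Missing data will be removed on a per-protocol basis, with a statistical analysis significance level set at .05".
- Noncompleter check: "Demographic information (ie, age, gender, and race) will be assessed between groups and program noncompleters", by independent-sample t tests.
- Second look at non-completion: "An intention-to-treat analysis will be completed to assess whether the outcome of treatment impacts participants’ likelihood of not completing the program".
- Arm comparison: a 2×3 repeated measures ANOVA for each questionnaire, and also a linear mixed-effects model with a random effect for patient and "fixed effects as treatment, time, and their interaction".

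The text does not say whether the mixed model is fitted before or after the removal of missing data.

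**The concern.** A plan that drops participants with missing data needs to show who was dropped. In an anxiety trial, symptom severity, depression and quality of life at entry are obvious candidates for affecting both leaving the program and the week-12 score. They matter more if they act differently in the two arms. That is plausible here: the trial is open-label, and weekly modules with homework ask more of participants than replies to chat prompts.

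The protocol names the variables for its noncompleter comparison, and they are demographic only. Age, gender and race could look similar while those who left one arm were more anxious or more depressed at entry. A reader of the trial report would then have no baseline evidence on severity with which to judge the completers-only result.

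**Working it through.** **The plan's own figure.** The only computable figure in the section is 50 per arm for an effect of 0.5, power 0.8 and α .05.
- One-sided: n = 2 × ((1.645 + 0.842)/0.5)² = 49.5, so 50.
- Two-sided: n = 2 × ((1.960 + 0.842)/0.5)² = 62.8, so 63.

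The figure reproduces only one-sided or with baseline adjustment. That is a separate matter. Here 0.5 serves only as a yardstick.

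**What the demographic check can show.** If demographics are unrelated to severity, three independent tests at .05 are all non-significant with probability 0.95³ = 0.857, whatever the severity gap. In simulation with N = 100, 20–40% noncompleters and a true baseline severity gap of 0.5–0.8 SD:

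| Assumed correlation of demographics with severity | All three tests non-significant |
|---|---|
| 0 | about 85–87% of trials |
| 0.1 | 82–86% |
| 0.3 | 58–77% |

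Unless the correlation is substantial, a clean result says almost nothing about severity.

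**Possible size of the shift.** Assumptions, none from the documents:
- 30% noncompletion per arm, related to severity in one arm only;
- noncompleters worse at baseline by g = 0.38, 0.60 or 0.78 SD on the scale that drives dropout;
- all correlations among baseline anxiety, baseline depression and week-12 anxiety equal to 0.5.

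Among completers in the affected arm, the mean of the driving scale moves by −0.30g.

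*Dropout follows the scale's own baseline.*
- Week-12 shift = 0.5 × (−0.30g) = −0.15g, which gives −0.06, −0.09, −0.12 SD.
- Change-score shift = −0.15g + 0.30g = +0.15g, which gives +0.06, +0.09, +0.12 SD.
- After own-baseline adjustment (slope 0.5): −0.15g + 0.5 × 0.30g = 0.

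Against 0.5, the shift is 0.06/0.5 = 12% to 0.12/0.5 = 24%.

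*Dropout follows another scale, such as depression.*
- Baseline anxiety and week-12 anxiety both move by −0.15g, so the change score is unbiased in this symmetric set-up.
- Adjusted for own baseline only: −0.15g + 0.5 × 0.15g = −0.075g, about −0.03 to −0.06 SD.
- Adjusted for both baselines (slopes 1/3 each): −0.15g + 0.15g/3 + 0.30g/3 = 0.

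*Dropout related to severity equally in both arms.* The two shifts cancel and the arm difference moves by about 0.

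A simulation with 2,000,000 draws per arm agrees with these expressions to within about 0.003 SD.

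**Power of a severity comparison (two-sided t test, .05).**

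| Comparison | Gap | Power |
|---|---|---|
| Pooled, 30 vs 70 | 0.5 SD | 0.62 |
| Pooled, 30 vs 70 | 0.6 SD | 0.78 |
| Pooled, 30 vs 70 | 0.8 SD | 0.95 |
| Within one arm, 15 vs 35 | 0.6 SD | 0.48 |
| Pooled, 0.6 SD gap in one arm only (pooled gap 0.3 SD) | 0.3 SD | 0.28 |

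Significance tests are therefore a poor basis for the by-arm comparison.

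**The case against.** **The list need not be exhaustive.** The parenthesis defines what counts as demographic information. It does not say that noncompleters will be compared on nothing else, and an article may leave the contents of an attrition table to a fuller document. This has some force. But the article did specify the check and its variables, so an analysis plan that followed it would carry the same gap.

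**The harm comes from elsewhere.** The 0.06–0.12 SD shift arises from removing missing data before the ANOVA. A longer attrition table leaves that estimate unchanged, and nothing makes the check a gate for later analyses. This stands. The table lets a reader judge the result; only the added model offers a different estimate.

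**The mixed model already protects.** Fitted to all observed data, it largely covers dropout explained by the scale's own scores, and week-6 data would help further. But the text does not exempt it from the removal, and its fixed effects do not include the other scales' baselines.

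**Stronger readings.** A reader might infer that nothing else is planned on non-completion. The text does not support that: the sentence labelled intention-to-treat is a second look, although it concerns treatment outcome rather than baseline severity. Nor is arm ignored, because the quoted sentence compares the groups; only a noncompleter breakdown by arm is unstated. A reader might also infer that the trial's arm difference will be biased. That needs severity-related dropout that differs between arms, and nothing in the documents shows it.

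**The residual is small.** With 35 completers per arm, the standard error of a raw arm difference is √(2/35) = 0.24 SD, so 0.03–0.06 SD is about 0.13–0.25 standard errors. This stands and limits the weight of the point.

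**Conclusion.** The point holds as an inexpensive improvement. The stated baseline comparison of noncompleters is confined to demographics, the plan removes missing data, and the informative baseline scores are already in hand. The comparison as written says little about severity-related attrition.

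The numerical effect is illustrative and modest, and it depends on the assumed dropout rate, severity gap and correlations, and on dropout that differs between arms. The shift ranges from about 0, when the relation is the same in both arms, to about 0.12 SD, when it is present in one arm only and follows the scale's own baseline. The case for the change is that it makes the attrition report informative. It does not establish that the planned arm comparison is wrong.

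**What to change.** 1. Extend the noncompleter sentence: compare completers and noncompleters, overall and by arm, on baseline STAI, Q-LES-Q-SF, GAD-7 and DASS-42 as well as age, gender and race. Report standardized differences rather than relying on significance tests, given the power of about 0.48 within an arm.

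2. Add one prespecified sensitivity linear mixed-effects model per questionnaire, fitted to all observed data without the per-protocol removal, with all four baseline scores as fixed covariates. Take weeks 6 and 12 as the responses, so that a scale's own baseline is not both outcome and covariate.

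3. Fix the covariate set in advance. Choosing scores by their association with non-completion would mean eight tests (four scales, two arms), with a chance of at least one false trigger of up to 1 − 0.95⁸ = 0.34 if independent.

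The cost is a sentence or two of wording and a few more lines of analysis. No new data, visits or participants are needed.

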**Methods:**

We will randomly allocate participants (N=100) who are 18 years or older with a confirmed diagnosis of GAD to either an e-CBT program or a mental health check-in program over 12 weeks to address their anxiety symptoms. Participants in the e-CBT arm will complete predesigned modules and homework assignments while receiving personalized feedback and asynchronous interaction with a therapist through the platform. Participants in the mental health check-in arm will be contacted weekly through the web-based platform’s written chat feature (messaging system). Therapists will ask the participants a series of predesigned questions that revolve around a different theme each week to prompt conversation. Using clinically validated questionnaires, the efficacy of the e-CBT arm will be compared to the mental health check-in arm. These questionnaires will be completed at baseline, week 6, and week 12.

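### The 2×3 repeated measures ANOVA counts baseline as an outcome visit and leaves the deciding effect unnamed; a baseline-adjusted week-12 difference would be clearer and usually more efficient, at no cost

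*Protocol article*

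**What the plan says.** The Methods paragraph of the abstract fixes the visits: "These questionnaires will be completed at baseline, week 6, and week 12". Outcome Evaluation and Analysis agrees: after the baseline assessment the four scales "will be completed again during week 6 and week 12". For the between-arm comparison, that section states that a 2×3 "repeated measures ANOVA will be completed for each questionnaire score at the time points to investigate the differences between the 2 groups". It adds linear mixed-effects models with "random effects as patient identification and fixed effects as treatment, time, and their interaction". The Results section mentions linear and binomial regression and names no covariates.

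On size, the article states that "a sample of 50 participants in each group was determined to be sufficient", namely "sufficient for an effect size of 0.5", with power 0.8 and α .05. It does not give the type of effect size, the sidedness, the SD or the correlation between visits.

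**The concern.** The primary objective is to compare the efficacy of two 12-week programmes, and the natural summary is the between-arm difference at week 12. In a 2×3 ANOVA the third time level can only be baseline. Under 1:1 randomisation the expected baseline difference is zero.

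- The group effect averages that zero with the two follow-up differences, so it estimates a fraction of the week-12 effect.
- The group-by-time interaction asks whether the three differences are unequal. It has 2 degrees of freedom and by itself gives neither a direction nor a week-12 difference.
- The text does not say which of the two answers the objective.

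No model in the article is described as adjusting for baseline, although every scale is measured then. At stake are some power and a clear primary estimate.

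**Working it through.** **The plan's own figure.** For two means, n per arm = 2(z_α + z_β)²/d² with d = 0.5.

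- One-sided .05: 2(1.645 + 0.842)²/0.25 = 49.5, so 50. This matches.
- Two-sided .05: 2(1.960 + 0.842)²/0.25 = 62.8, so 63. At 50 per arm, exact t power is 0.697.

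The stated size therefore corresponds to a one-sided comparison of two groups at a single time point. The remaining figures are two-sided.

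**Inputs.** From the article: 50 per arm, 1:1 allocation, three visits, effect 0.5 (read as SD units), α .05. Assumed because not given: SD 1 at each visit, the same correlation ρ between every pair of visits, no dropout, and either a linear profile (0, 0.25, 0.5) or an early plateau (0, 0.5, 0.5) at baseline, week 6 and week 12.

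**What the group effect estimates.** Linear: (0 + 0.25 + 0.5)/3 = 0.25 SD. Plateau: (0 + 0.5 + 0.5)/3 = 0.33 SD. This does not depend on ρ.

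**Formulas** (√(n/2) = √25 = 5):

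- Group effect: noncentrality = 5 × mean effect / √((1 + 2ρ)/3), 98 df. Linear, ρ = 0.5: 5 × 0.25/0.816 = 1.53.
- Interaction: λ = 25 × Σ(e − ē)²/(1 − ρ), where e are the three visit differences and ē their mean; 2 and 196 df. Linear, ρ = 0.5: 25 × 0.125/0.5 = 6.25. Plateau: 25 × 0.1667/0.5 = 8.33.
- Week-12 change-from-baseline contrast, which the mixed model could supply: 5 × 0.5/√(2(1 − ρ)), 98 df. ρ = 0.5: 2.50.
- Baseline-adjusted week-12 contrast: 5 × 0.5/√(1 − ρ²), 97 df. ρ = 0.5: 2.89.

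**Power:**

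| Test | Profile | ρ = 0.3 | ρ = 0.5 | ρ = 0.7 |
|---|---|---|---|---|
| Group effect | linear | 0.40 | 0.33 | 0.28 |
| Group effect | plateau | 0.62 | 0.52 | 0.45 |
| Interaction, 2 df | linear | 0.45 | 0.60 | 0.83 |
| Interaction, 2 df | plateau | 0.57 | 0.73 | 0.92 |
| Change contrast, week 12 | either | 0.55 | 0.70 | 0.89 |
| Baseline-adjusted, week 12 | either | 0.74 | 0.82 | 0.93 |

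**Where the gain disappears.** With a plateau and ρ = 0.8, the interaction has 0.987 and the adjusted contrast 0.985. In a simulation (4,000 runs) with correlations 0.7 (baseline–week 6), 0.7 (week 6–week 12) and 0.5 (baseline–week 12) and a plateau, they have 0.82 and 0.81.

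**When adjustment reaches 80%.** By the normal approximation, 62.8 × (1 − ρ²) = 50 gives ρ of about 0.45. At ρ = 0.3 the same formula needs 58 per arm.

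**The case against.** The strongest defence is that the plan already contains a usable answer. The article does not say that the ANOVA group effect decides the trial, and in such a design the interaction is the term that tests whether change differs by arm. The mixed model, with "fixed effects as treatment, time, and their interaction", includes (with time as categories) a directional 1-df contrast of week-12 change, which allows for chance baseline imbalance. Covariates and contrasts are also details that a condensed article may leave to a fuller document. Much of this stands.

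It rules out several stronger readings that a reader might infer:

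- *The trial has 33% power.* That figure needs the group effect to be the test, a linear profile and ρ = 0.5. The documents state none of these.
- *The planned tests are invalid.* Under randomisation they keep their type I error; no fault of that kind arises here.
- *The plan cannot address week 12.* The mixed model can, though less efficiently than with baseline adjustment.
- *Adjustment restores full power.* The gain depends on a correlation and a week-6 effect that are not given. At ρ = 0.3 the adjusted contrast still has only 0.74, and dropout would lower every figure. Part of the two-sided shortfall comes from the sample size, which is a separate matter.

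What the defence does not remove: the ANOVA is a stated choice, it uses baseline as an outcome level, and its deciding effect is not named. The mixed model as described has neither a baseline covariate nor a common-baseline constraint. With categorical time, a random intercept only and complete data, its treatment and interaction tests coincide with those of the ANOVA.

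**Conclusion.** The point holds as a recommended improvement, not as an error that must be corrected. The dilution of the group effect to 0.25–0.33 SD is arithmetic, given a true 0.5 SD difference at week 12 and a week-6 difference between half and all of it.

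The efficiency loss is conditional on 50 completers per arm, two-sided .05, SD 1 and equal correlation. Over ρ from 0.3 to 0.7, baseline adjustment gains 0.19 down to 0.04 in power over the mixed-model change contrast (0.74 − 0.55; 0.93 − 0.89). Over the interaction it gains between 0.29 (0.74 − 0.45; linear, ρ = 0.3) and 0.01 (0.93 − 0.92; plateau, ρ = 0.7). Where that gain is negligible, the adjusted contrast still supplies a directional week-12 estimate, which the omnibus test does not.

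**What to change.** Name one primary analysis: the baseline-adjusted between-arm difference at week 12 with its 95% CI. Fit a mixed model to the week-6 and week-12 scores with baseline score, arm, visit, arm-by-visit and baseline-by-visit as fixed effects. Alternatively, keep the planned mixed model with baseline as a visit and constrain the arms to a common baseline mean. Treat week 6 as secondary. If the ANOVA is kept, label it supportive and say which effect is read. Quote any power gain as a range over assumed correlations, not as a single figure.

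The cost is a change of wording before the analysis. It needs no further participants, visits or questionnaires, and the mixed-model procedure in SPSS, the software already planned, is sufficient.

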### Objectives

The primary objective will be to compare the efficacy of an e-CBT program to a web-based mental health check-in program. Additionally, the individual effects of each treatment will be evaluated using clinically validated symptomology questionnaires.

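### Four questionnaires are each tested at .05 for one efficacy objective with no primary named; if any one positive scale counts, the false-positive chance is about 9–19%, not 5%

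*Protocol article*

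**What the plan says.** The Objectives section states: "The primary objective will be to compare the efficacy of an e-CBT program to a web-based mental health check-in program". It gives no instrument and no time point. The abstract's Methods paragraph is equally general: "Using clinically validated questionnaires, the efficacy of the e-CBT arm will be compared to the mental health check-in arm".

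The section Outcome Evaluation and Analysis lists four questionnaires at baseline and adds: "The STAI, Q-LES-Q-SF, GAD-7, and DASS-42 will be completed again during week 6 and week 12". For the comparison of the arms, a 2×3 "repeated measures ANOVA will be completed for each questionnaire score at the time points". The threshold is given once, for everything: "with a statistical analysis significance level set at .05". A second model is applied to the same scores: "Data will also be assessed with linear mixed-effects models", with no statement of which of the two governs.

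The same section justifies the sample size of 50 per group from these inputs: "effect size of 0.5, a power of 0.8, and an α of .05". The questionnaire and visit to which the 0.5 applies are not given.

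**The concern.** The design inputs and the test plan do not match. The power statement has one effect size and one alpha, which fits one comparison. The analysis paragraph then specifies four comparisons, each at the full .05, and all serve the same primary objective. Nothing says which of the four decides, whether all must agree, or what happens if they disagree.

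The scales do not all measure the same thing. By their names, they cover state and trait anxiety, quality of life, generalized anxiety, and depression with anxiety and stress, so divergent results are plausible. A report could then present whichever scale crossed .05 as the efficacy result without departing from the published text. In that case the 5% level would not protect the trial's main conclusion.

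**Working it through.** **Inputs from the article (Outcome Evaluation and Analysis).** Four questionnaires; one 2×3 repeated measures ANOVA for each; level .05, sidedness not stated; 50 per group; effect size 0.5; power 0.8.

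**Assumed, because the article does not give them.** (a) Any one significant questionnaire is read as efficacy. (b) A common correlation ρ between the four test statistics, varied from 0 to 0.9.

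**Step 1: the plan's own sample size (normal approximation, two groups).** n per group = 2(z_α + z_β)² / d², with d = 0.5 and z_β = 0.842.
- Two-sided: 2(1.960 + 0.842)² / 0.25 = 62.8, so 63 per group.
- One-sided: 2(1.645 + 0.842)² / 0.25 = 49.5, so 50 per group.

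The stated 50 is therefore reproduced for a single one-sided test. With 50 per group the expected z is 0.5 × √(50/2) = 2.5. Two-sided power is Φ(2.5 − 1.960) = Φ(0.54) = 70.5% (69.7% with the t distribution). One-sided power is Φ(2.5 − 1.645) = 80.4%.

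**Step 2: four independent tests.** 1 − (1 − 0.05)⁴ = 1 − 0.8145 = 18.5%.

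**Step 3: four correlated tests.** With c = 1.960, the chance of at least one false positive is

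1 − ∫ φ(u) [Φ((c − √ρ·u)/√(1−ρ)) − Φ((−c − √ρ·u)/√(1−ρ))]⁴ du.

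| Assumed ρ | At least one false positive, each test at .05 | Same, each at .0125 |
|---|---|---|
| 0 | 18.5% | 4.9% |
| 0.3 | 17.4% | 4.7% |
| 0.5 | 15.6% | 4.3% |
| 0.7 | 13.0% | 3.7% |
| 0.8 | 11.4% | 3.2% |
| 0.9 | 9.4% | 2.6% |

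**Step 4: check on the planned analysis itself.** The 2×3 ANOVA was simulated under no effect (50 per arm, four outcomes, assumed correlation of 0.5 between visits, 20,000 runs). One questionnaire alone gave about 5% for the group-by-time test. At least one of four gave 18.4% (ρ = 0), 15.5% (0.5), 13.1% (0.7) and 11.8% (0.8). This agrees with Step 3.

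**Step 5: what the range leaves out.** It counts one test per questionnaire. The article does not say whether the group effect or the group-by-time term decides. If either counted, the same simulation gives 34% at ρ = 0, 25% at 0.7 and 22% at 0.8. The mixed models, and the regressions announced in the Results section, are further routes that are not counted here.

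**The case against.** The strongest reply is that this is a condensed article. Multiplicity handling is often left to the full protocol or a statistical analysis plan, and the article cites a registry record that is not among the documents reviewed. A primary outcome may already be fixed there. This stands as a limit on the point: one cannot conclude that the trial has no primary outcome anywhere. It does not dispose of the point, because the article does more than stay silent. It fixes one test per questionnaire at a common .05 for a single primary objective, beside a power statement built for one comparison.

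The second reply is that the inflation needs a success rule that the article never states. This also stands. If all four scales had to be significant, the error would not exceed 5%. The article excludes neither reading, so the figure must be given as conditional.

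Some stronger readings are tempting but not supported:
- A reader might take 13–19% as the error rate. The lower end assumes a correlation no higher than 0.7, which the article does not justify. At 0.8 to 0.9 the figure is 11.4% to 9.4%.
- A reader might count seven scales by splitting the STAI into two parts and the DASS-42 into three, giving 1 − 0.95⁷ = 30%. The article plans a test for each questionnaire score and announces no subscale tests.
- A reader might count week 6 and week 12 as separate tests. The planned ANOVA takes all three time points together.
- A reader might add the open-label design and self-reported outcomes to the case. Those concern bias, not the familywise error rate.

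**Conclusion.** The point holds in conditional form. As published, four questionnaires are each tested at .05 for one efficacy objective, with no primary outcome, hierarchy or adjustment. If any one significant questionnaire is taken as efficacy, the chance of at least one false positive is about 9–19%, for assumed correlations from 0.9 down to 0. Even at the lower end this is nearly double the nominal 5%. With one named primary and one deciding test it is 5%.

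The facts about the text and the arithmetic are firm. The success rule and the correlations are assumptions, and a registry record or analysis plan not shown here could resolve the matter.

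**What to change.** Before any between-arm data are seen, and with the date of the decision disclosed, name one primary questionnaire, one time point and one contrast. The Results section reports 50 participants already recruited to an open-label trial, so an undated choice could itself look post hoc. If the registry record names a primary outcome, use that one. If not, one option is GAD-7 at week 12, from the mixed model already planned, tested two-sided at .05. The article does not rank the scales, so this is an example and not something the text implies.

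Label the other questionnaires and the week-6 results secondary. Either test them with a Holm adjustment, or report them as estimates with confidence intervals and no efficacy claim.

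Tie the power statement to the primary and restate it. At effect size 0.5 and two-sided .05, 50 per group gives about 70% in a simple two-group comparison, and 63 per group would be needed for 80%. The use of baseline data changes this, by an amount that depends on the baseline-to-follow-up correlation r, which the article does not give. If the 0.5 is in units of the raw standard deviation, a baseline-adjusted comparison needs 58 per group at r = 0.3, 48 at 0.5 and 33 at 0.7 (variance factor 1 − r²). A change-from-baseline contrast needs 88, 63 and 38 (variance factor 2(1 − r)). The restated power should say which contrast and correlation it assumes. None of these figures allows for dropout.

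The cost is a few sentences and no new data. The other scales can no longer carry the efficacy claim alone, and in a simple two-sided comparison the stated power becomes less favourable.
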